### Study endpoints

#### Primary

The primary endpoint is the difference in plasma levels of IL-6 when comparing patients anesthetized with sevoflurane versus propofol.

#### Secondary

The secondary endpoints are (1) the differences in levels of other proinflammmatory and anti-inflammatory mediators in blood, subcutaneous tissue, and visceral adipose tissue, namely (a) inflammatory mediators associated with neutrophils: metalloprotease (MMP)-2 [36–38], MMP-9 [36], CXCR2 [39], IL-12 [40], CCL3 (macrophage inflammatory protein (MIP)-1α) [41–44], CCL2 (MCP1) [44], IL-1β [45], TNF-α [46], NRF2 [47, 48], (b) mediators associated with macrophages: proinflammatory (IL-1β, CD40 [49], CD80 [50]), M1 phenotype markers (TNF-α, IL-6 [51–53], iNOS [54–56]), anti-inflammatory (IL-1 receptor antagonist (IL-1RA) [57–59], NrF2), M2 phenotype markers (CD163 [60, 61], CD206 [62], arginase [63, 64], IL-10 [65], transforming growth factor (TGF)-β1 [66–68]), and (c) mediators associated with cell death pathways (BCL2-associated X (Bax), bcl2 [69, 70], caspases 3 and 9 [71–73]); (2) intraoperative complications: (a) hypoxemia (PaO_2_/FiO_2_ ratio < 300), (b) hypotension (systolic blood pressure < 90 mmHg), (c) bradycardia (heart rate < 50 bpm), (d) unexpected need for intensive care unit (ICU) admission or readmission, (e) length of hospital stay, (f) number of days at home in the first month after surgery, and (g) postoperative complications: pulmonary infection (defined as new or progressive radiographic infiltrate and at least two of the following criteria - antibiotic treatment, axillary temperature > 38 °C, leukopenia (WBC < 4000 cells/mm^3^) or leukocytosis (WBC > 12,000 cells/mm^3^), and/or purulent secretions); sepsis (defined as suspicion or certainty of infection and an acute increase ≥ 2 points in the Sequential Organ Failure Assessment Score (SOFA) in response to an infection, representing organ dysfunction); septic shock (defined as sepsis plus need for vasopressor to maintain mean blood pressure > 65 mmHg plus lactate > 2 mmol/L [18 mg/dL] after adequate volume resuscitation [74–76]); extrapulmonary infection (of the operative wound or any other infection); coma (Glasgow Coma Scale < 8 in the absence of therapeutic sedation); acute myocardial infarction (according to the universal definition thereof [77]); acute kidney failure (according to the risk, injury, failure, loss, end-stage renal failure (RIFLE) criteria classification system [78]); DIC (according to the International System for the Evaluation of Thrombosis and Hemostasis for DIC [79]); GIF (defined according to the GIF score [80]); acute liver failure (defined as a ratio of total bilirubin on the 5th postoperative day to the 1st postoperative day > 1.7 plus a ratio of international normalized ratio (INR) on the 5th postoperative day to the 1st postoperative day > 1.0 or presence of hepatic encephalopathy and INR > 1.5) [81, 82].

## Statistical analysis

Positive modulation of the IL-6 receptor and IL-6 expression in adipose tissue is known to occur in obesity [51, 83]. A convenience sample of 48 patients has been chosen on the basis of a study in which plasma IL-6 levels were compared before and after anesthesia in patients undergoing thoracic surgery with one-lung ventilation [84]. The sample size was calculated using G*Power 3.1.9.2 software (University of Dusseldorf, Germany), taking into account an effect size of 1.33, a two-sided test, and a ratio of 1. A sample size of 10 patients in each group will provide adequate power (80%), assuming α = 0.05, to detect at least an effect size of 33% difference in IL-6 levels in plasma samples collected immediately after induction of anesthesia and before extubation in obese patients anesthetized with sevoflurane or propofol (*p* = 0.05). Considering possible losses and to obtain even more significant results, we chose to increase the sample to 24 patients per group. Data will be tested for normality and variability. Comparison of the parameters of interest between participants in the sevoflurane and propofol groups will be performed by Student’s *t* test or the Wilcoxon test, as appropriate. Statistical significance will be accepted at *p* < 0.05. All analyses will be undertaken by an independent statistician, who will be blinded to group allocation.

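### The stated 80% power for a 33% difference in IL-6 was calculated for 1.33 standard deviations, and no mean, SD or CV links the two

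*Protocol article*

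**What the plan says.** All of this stands in one paragraph of the protocol article, under Statistical analysis.

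- The program and its inputs: "The sample size was calculated using G*Power 3.1.9.2 software", "taking into account an effect size of 1.33, a two-sided test, and a ratio of 1", and "assuming α = 0.05".
- The result: 10 patients per group, 80% power.
- The effect that this power is said to apply to: "to detect at least an effect size of 33% difference in IL-6 levels in plasma samples collected".
- The basis for the assumption: a study in which "plasma IL-6 levels were compared before and after anesthesia in patients undergoing thoracic surgery with one-lung ventilation". No IL-6 mean, SD, CV or log-scale SD is reported from it.
- The final size: besides allowing for losses, "to obtain even more significant results, we chose to increase the sample to 24 patients per group". No power or detectable difference is given for 24 per group.
- The test: group comparisons "will be performed by Student’s *t* test or the Wilcoxon test, as appropriate". No transformation of IL-6 is mentioned.

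**The concern.** Two consecutive sentences describe one calculation but name its effect in different units. In a G*Power two-sample t test, an effect size of 1.33 is a difference of 1.33 standard deviations. A 33% difference is relative to a mean. Converting one into the other needs the ratio of SD to mean, and the article does not give it.

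The power claim concerns the primary endpoint. A reader who takes it at face value will treat a non-significant result as evidence against a 33% difference in IL-6, because the trial enrols more than twice the number said to be enough. Whether the design can bear that reading depends entirely on a variability figure that is not stated. The Background also says that the trial is meant to inform later sample size calculations, so the units of the effect should be unambiguous.

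**Working it through.** **Inputs.** From Statistical analysis: effect size 1.33, two-sided α = 0.05, allocation 1:1, 10 per group, 80% power, a stated 33% difference, and a final 24 per group. Not in the document, so assumed: the between-patient CV of IL-6 (SD/mean), taken from 25% to 100%, with the same SD in both arms; and 20 evaluable per group as an illustration of losses.

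**1. Reproduce the stated figure.** Two-sample t test with n per group, df = 2n − 2, noncentrality δ = d·√(n/2). Power is the probability that a noncentral t variate with these parameters exceeds the two-sided 5% critical value in absolute size.

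- n = 10, d = 1.33: df = 18, δ = 1.33·√5 = 2.97, power 80.3%.
- n = 9, d = 1.33: df = 16, δ = 1.33·√4.5 = 2.82, power 75.5%.

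So 10 per group is exactly the minimum for 80%. Other tests with d = 1.33 do not fit: a one-sided t test reaches 80% at 8 per group (81.1%), a paired t test needs 7, and a Wilcoxon rank-sum test on normal data has 78.2% at 10. The calculation was a two-sided, two-sample t test for 1.33 SD.

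**2. When do 1.33 SD and 33% agree?** On the raw scale d = 0.33/CV. Setting d = 1.33 gives CV = 0.33/1.33 = 24.8%.

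**3. Power for a 33% difference over a range of CVs** (raw scale, d = 0.33/CV):

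| Assumed CV | d | Power, 10 per group | Power, 24 per group | n per group for 80% |
|---|---|---|---|---|
| 25% | 1.32 | 80% | 99% | 11 |
| 40% | 0.825 | 42% | 80% | 25 |
| 50% | 0.66 | 29% | 61% | 38 |
| 75% | 0.44 | 15% | 32% | 83 |
| 100% | 0.33 | 11% | 20% | 146 |

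**4. Does the scale matter?** If IL-6 were analysed as logarithms, the SD would be √ln(1 + CV²) and d = |ln(ratio)|/SD. Power with 24 per group:

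| Assumed CV | 33% increase (ratio 1.33) | 33% reduction (ratio 0.67) |
|---|---|---|
| 50% | 53% | 82% |
| 75% | 30% | 53% |
| 100% | 21% | 37% |

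So the scale and the direction of the 33% matter as well as the CV, and the article fixes none of the three.

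**5. What the planned sample delivers.** Solving for the d that gives 80% power: 1.32 SD at 10 per group, 0.91 SD at 20, 0.83 SD (0.826) at 24. For 1.33 SD itself, 24 per group gives 99.5% power.

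Expressed as ratios, 0.826 SD at CVs of 50%, 75% and 100% is:

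- raw scale, 1 + 0.826·CV: 1.41, 1.62 and 1.83;
- log scale, exp(0.826·√ln(1 + CV²)): 1.48, 1.74 and 1.99.

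**The case against.** The strongest reply is that nothing was miscalculated. Ten per group is right for an effect size of 1.33, and a 33% difference equals 1.33 SD if the CV is about 25%. The mean and SD may stand in the cited study or in the full protocol that this article condenses. The trial also enrols 24 per group rather than 10, which supports 33% on the raw scale up to a CV of about 40% (0.33/0.826). Finally, the article calls the sample a convenience sample and the trial a non-conclusive pilot.

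Much of this stands. The fault lies in describing the effect, not in the arithmetic, and it changes neither the sample size nor the test. But the article chose to state effect, power and n together, and as printed they do not connect. Being a pilot does not settle that, because the paragraph still makes a formal 80% power claim on the primary endpoint.

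A reader might infer more than the document supports:

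- **That 1.33 was misread as a ratio (1.33 − 1 = 33%).** This is plausible, but the article does not show how the 33% arose.
- **That a within-patient, before-and-after effect was used to size a between-arm comparison.** The article says what the cited study compared. It does not say that 1.33 is the within-patient effect, and the study is not available here.
- **That 33% meant 0.33 SD**, giving 10.8% power at 10 per group and 146 per group needed. This is the least natural reading of a percentage difference in IL-6 levels and should not be the headline. The same figures appear in the table only as the case of a 100% CV.

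**Conclusion.** The point holds in this form: the 80% power belongs to a between-group difference of 1.33 SD, and its restatement as a 33% difference is unsupported because no mean, SD or CV is given. It would be too strong to call the 33% impossible, or to say that the trial is shown to be underpowered for it. Actual power for 33% cannot be fixed from the document. On the raw scale it runs from 80% to 11% at 10 per group, and from 99% to 20% at 24 per group, over assumed CVs of 25% to 100%. The planned 24 per group reaches about 80% for a 33% raw-scale difference only if the CV is about 40% or less.

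What can be said without a CV is that 24 per group has 80% power for 0.83 SD, or 0.91 SD with 20 evaluable. These figures assume a t test on roughly normal data with equal SDs. Unless the missing variability figure is supplied and supports it, a non-significant result should not be read as excluding a 33% difference in IL-6.

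**What to change.** Reword the paragraph in one of two ways.

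1. **SD units.** Keep the 10-per-group result but give its effect as 1.33 SD instead of 33%. Add that the planned 24 per group gives 80% power (two-sided 5% t test) for a between-group difference of 0.83 SD, or 0.91 SD if 20 per group are evaluable.
2. **Percentage.** Keep 33%, give the assumed IL-6 mean and SD with their source, name the analysis scale and the direction of the difference, and recompute power at 24 per group.

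If detectable ratios are quoted, name the scale, since the raw and log values in step 5 of the working differ. In either case, delete the hope of more significant results as a reason for 24 per group and keep the allowance for losses. Add that a non-significant result does not by itself exclude a 33% difference.

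The cost is the rewording of one paragraph. No extra patients are needed, and the endpoint and test stay as they are. The stated detectable difference becomes less favourable.

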**Methods/design:**

The OBESITA trial is a prospective, nonblinded, single-center, randomized, controlled clinical pilot trial. The trial will include 48 patients with a body mass index ≥ 35 kg/m^2^, scheduled for laparoscopic bariatric surgery using sleeve or a Roux-en-Y gastric bypass technique, who will be allocated 1:1 to undergo general inhalational anesthesia with sevoflurane or total intravenous anesthesia (TIVA) with propofol. The primary endpoint is the difference in plasma interleukin (IL)-6 levels when comparing the two anesthetic agents. Blood samples will be collected prior to anesthesia induction (baseline), immediately after anesthetic induction, and before endotracheal extubation. Levels of other proinflammatory and anti-inflammatory cytokines, neutrophil chemotaxis, macrophage differentiation, phagocytosis, and occurrence of intraoperative and postoperative complications will also be evaluated.

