### Samples

Blood (15 mL) will be collected in heparinized tubes prior to induction of anesthesia (baseline), immediately after anesthetic induction (T1), and before extubation (T2).

Two small fragments of subcutaneous adipose tissue and visceral adipose tissue will also be sampled. Each fragment will measure 2 × 2 × 2 cm after excess blood vessels and connective tissue have been removed with the aid of a scalpel, and will be obtained from surgical specimens that would be discarded immediately following gastroplasty.

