There are several patient-related (and thus nonmodifiable) factors associated with increased incidence of postoperative complications after bariatric surgery: male sex, preoperative BMI ≥ 60 kg/m^2^, open surgery, smoking within the last year, deep vein thrombosis, therapeutic anticoagulation, and serum albumin < 3.5 g/dL [91]. The duration and invasiveness of the surgical procedure may affect the inflammatory response, thus increasing the risk of bias [91], and will therefore be taken into account in this trial; these factors will be individually analyzed post hoc to isolate their interference with the outcomes of interest. The role of positive end-expiratory pressure (PEEP) in mechanical ventilation during general anesthesia for surgery remains uncertain. An ongoing randomized clinical trial is testing two different levels of PEEP: 4 cmH_2_O without recruitment maneuvers versus 12 cmH_2_O with recruitment maneuvers [35, 92]. In the present trial protocol, a PEEP of 5 cmH_2_O is suggested based on a secondary analysis of the international multicenter LAS VEGAS study, restricted to obese patients [93].

To our knowledge, only one prospective study has compared the effect of anesthesia with sevoflurane on inflammation to that of TIVA with propofol, in 54 adults undergoing thoracic surgery with one-lung ventilation [22]. The authors observed that the increase in inflammatory mediators such as TNF-α, IL-6, and monocyte chemoattractant protein 1 (MCP-1) was significantly blunted in the sevoflurane group. Sevoflurane was also associated with fewer postoperative adverse events [22]. A randomized controlled trial of 5400 patients, which compared volatile anesthetics to TIVA for elective cardiac surgery, showed that anesthesia with a volatile agent did not result in a significantly lower 1-year mortality rate compared to TIVA [94].

Moreover, in the experimental setting of obesity, a 1-h infusion of propofol resulted in increased airway resistance, atelectasis, and pulmonary inflammation mediated by increased TNF-α and IL-6 in lung tissue, with depletion of antioxidative enzymes [17]. Based on this evidence, we hypothesize that anesthesia with sevoflurane will result in a weaker inflammatory response compared to anesthesia with propofol.

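### The stated IL-6 comparison has no baseline term and lets a normality check choose the test; a prespecified baseline-adjusted model would be more precise

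*Protocol article*

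**What the plan says.** The primary endpoint (Protocol article, Study endpoints, Primary) is worded without a time point or metric: "The primary endpoint is the difference in plasma levels of IL-6 when comparing patients anesthetized with sevoflurane versus propofol".

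The Statistical analysis section fixes the method. First, "Data will be tested for normality and variability". Then: "Comparison of the parameters of interest between participants in the sevoflurane and propofol groups will be performed by" one of two methods, a t test or a rank test; after naming the t test, the section leaves the choice open with the words "test or the Wilcoxon test, as appropriate". No covariate or transformation is named.

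The Samples section has blood drawn "prior to induction of anesthesia (baseline), immediately after anesthetic induction (T1), and before extubation (T2"), and the In vitro assays section confirms that this applies to all patients and that the plasma is used for IL-6. The power statement, however, refers to a "difference in IL-6 levels in plasma samples collected immediately after induction of anesthesia and before extubation in obese patients"; the pre-induction sample does not appear in it.

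On surgical factors, the Abstract admits patients "scheduled for laparoscopic bariatric surgery using sleeve or a Roux-en-Y gastric bypass technique". The Discussion accepts that duration and invasiveness of surgery may influence inflammation, and adds that "these factors will be individually analyzed post hoc to isolate their interference with the outcomes of interest".

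**The concern.** A measurement of the outcome taken before the anesthetic can act is usually the most useful covariate a small trial has. Here it is collected from everyone but has no place in the stated comparison. With 24 per arm, whatever part of the IL-6 variation is predictable from baseline stays in the error term.

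The second issue is the choice of test. If a normality check decides between a t test and a rank test, the trial does not know in advance whether it will report a mean difference or a shift in ranks. This matters for a trial whose Background section says it should inform later sample size calculations. A rank test chosen after the fact gives neither an effect in IL-6 units nor a baseline-adjusted residual SD.

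At stake is the precision and interpretability of the main result.

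**Working it through.** **Inputs from the article.** Effect size 1.33, two-sided α = 0.05, 80% power, ratio 1, 10 per group, raised to 24 per group (Statistical analysis).

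**Inputs assumed.** The article gives neither the correlation ρ between pre-induction and later IL-6 nor the spread of IL-6. The range ρ = 0.3, 0.5, 0.7 is used. The simulation takes log-normal IL-6 with a coefficient of variation of 75%, a true ratio of 0.67, and Shapiro-Wilk in each arm as the normality check.

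**Step 1: the plan's own figure.** Two-sample t test, noncentral t with noncentrality d√(n/2) and 2n − 2 degrees of freedom. For d = 1.33, n = 9 gives 75.5% power and n = 10 gives 80.3%. The stated 10 per group reproduces, so this point does not rest on an arithmetic error.

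**Step 2: what 24 per arm can detect without adjustment.** Solving the same formula for 80% power at n = 24 gives d = 0.826 SD.

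**Step 3: the alternatives.** Relative to unadjusted levels, and with equal variance at both times, the error variance is 1 − ρ² with baseline as a covariate (ANCOVA) and 2(1 − ρ) for a change score. The detectable difference scales with the square root of these factors; the ANCOVA column uses 45 degrees of freedom.

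| Assumed ρ | ANCOVA factor 1 − ρ² | Change factor 2(1 − ρ) | Detectable, ANCOVA | Detectable, change: 0.826 × √factor | Equivalent n per arm: 24/(1 − ρ²) |
|---|---|---|---|---|---|
| 0.3 | 0.91 | 1.40 | 0.79 SD | 0.98 SD | 26.4 |
| 0.5 | 0.75 | 1.00 | 0.72 SD | 0.83 SD | 32.0 |
| 0.7 | 0.51 | 0.60 | 0.59 SD | 0.64 SD | 47.1 |

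The change score cannot beat ANCOVA, because 2(1 − ρ) − (1 − ρ²) = (1 − ρ)² ≥ 0. It is worse than no adjustment when ρ < 0.5. Estimating the baseline slope, which the table ignores, inflates the variance by about 1 + 1/(48 − 4) = 1.02, or about 1% on the standard error. The gain over unadjusted levels therefore disappears once ρ² falls below about 0.02, that is, ρ below about 0.15.

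**Step 4: simulation of the stated rule, 24 per arm.**

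- Normality check, then t or Wilcoxon on levels: power about 0.51.
- t test on log levels: about 0.53.
- t test on log change: about 0.41 at ρ = 0.3 and 0.76 at ρ = 0.7.
- ANCOVA on log IL-6: about 0.56, 0.64 and 0.81 at ρ = 0.3, 0.5 and 0.7.
- Type I error: near 5% for both the stated rule and ANCOVA.
- Both arms passed the normality check in about 4% of runs. The t and Wilcoxon tests disagreed on significance in about 15%.

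**The case against.** The strongest objections, and what stands of each:

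- **Baseline is not shown to be thrown away.** A reader might infer that the plan discards pre-induction IL-6. The document does not support that: the endpoint does not say level or change, and a t test on change from baseline fits the wording. This stands. It also matters for size: at ρ = 0.7 the power gap to ANCOVA is 0.81 against 0.76 for a change score, not 0.81 against 0.51. It does not remove the point, since a change score is never more precise than ANCOVA and at ρ = 0.3 it does worse than ignoring baseline.
- **Validity is intact.** A reader might infer bias or an inflated false-positive rate. Neither follows. Allocation is randomized, chance baseline imbalance is already reflected in the unadjusted standard error, and type I error was near 5%.
- **The test choice may hardly vary.** With IL-6 as skewed as assumed, the check leads to the Wilcoxon test in about 96% of runs, and the article states no explicit decision rule. This stands as a limit on the practical effect. The estimand is still not fixed in advance.
- **The gain is assumed.** No correlation is given, and the simulated data suit the proposed model. At ρ = 0.3 the benefit is about two patients per arm, and part of the power gain comes from the log scale. The exclusion of patients with raised inflammatory markers could lower ρ. All of this stands.
- **A short article on a pilot.** Detail may be left to a fuller document. Here, however, the article does commit to a method, and that stated method is what is assessed.

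**Conclusion.** The point holds as one of efficiency and clarity. The article fixes a two-group t or Wilcoxon test with no baseline term, although the baseline is measured in everyone. On either reading of the endpoint this is expected to be less precise than a baseline-adjusted model. The detectable difference moves from 0.83 SD unadjusted to 0.79, 0.72 or 0.59 SD at assumed correlations of 0.3, 0.5 or 0.7, so the gain runs from small to substantial depending on a quantity the article does not give.

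Two further inferences about the surgical factors should not be drawn. One is that operative duration ought to be in the primary model. It is measured after randomization and the anesthetic could affect it, so leaving it outside the primary test is right. The other is that the announced post hoc analyses let the investigators choose their result: the two-group test remains the stated comparison. Surgical technique is a natural reading of invasiveness, but it is not the article's word, and the article does not list technique as a recorded variable.

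**What to change.** Make the primary analysis one prespecified linear model of log IL-6 at the pre-extubation sample (T2), with arm and log pre-induction IL-6 as terms. Naming T2 also settles the time point, which the endpoint leaves open. The covariate must be the pre-induction sample, not the post-induction one (T1), because the arms already differ in induction agent by then. Report the adjusted geometric mean ratio with its 95% confidence interval. Keep the Wilcoxon test as a sensitivity analysis, and stop using the normality check to select the test.

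If planned technique (sleeve or Roux-en-Y) is recorded before randomization, it may be added as a prespecified covariate in place of the post hoc analysis of invasiveness. Report operative duration by arm, outside the primary model.

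The cost is a wording change and one or two degrees of freedom. The core model needs no new data; technique would have to be confirmed as recorded.
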